### Evaluation Plan

Using the logic model as a foundation, the advisory committee and development team identified key areas that required evaluation. They prioritized metrics that would provide actionable insights for improving the app and its integration into existing campus mental health and wellness services. Drawing on their collective expertise, the committee discussed various data collection methods. They aimed for a mixed methods approach to capture both quantitative and qualitative data, ensuring a comprehensive evaluation. Moreover, recognizing the evolving nature of digital health interventions, the committee built in mechanisms for ongoing review and refinement of both the app and the evaluation process itself.

Throughout this process, the committee emphasized the importance of flexibility and adaptability, acknowledging that the evaluation plan may need to be adjusted as the project progresses and new insights emerge. They also stressed the need for ongoing communication and collaboration among all stakeholders involved in the implementation and evaluation of the student mental health and wellness app. The evaluation questions that could address important outcomes are listed below.

To what extent does the use of the mobile app lead to reductions in symptoms of anxiety, depression, and other common mental health issues among students?How many students download and actively use the app on a regular basis? What user characteristics or engagement patterns are associated with better outcomes?How well is the app integrated with campus counseling, health, and other support services? What are the facilitators and barriers to this integration?What are the key lessons learned from implementing the app, and what modifications or additional support are needed to sustain and scale the program in the long term?

Data collection methods will include pre-post surveys of app users to assess changes in knowledge regarding campus resources, presence and severity of mental health symptoms, emotional self-awareness, stigma and other barriers to care, confidence in and degree of help-seeking behaviors, and overall app usage data (downloads, login frequency, feature engagement). We also plan to conduct interviews and focus groups with app users, campus mental health staff, and other relevant stakeholders.

For continuous quality improvement, we plan to regularly review the evaluation results with the project team to identify the areas for app refinement and programmatic enhancements and use data to secure continued funding and support for sustaining and scaling the app-based program.

This evaluation plan (Table 1) outlines a mixed methods approach to assess the student mental health and wellness app project on multiple levels—individual student outcomes, community reach and usage, operational feasibility, and long-term sustainability. The plan emphasizes the importance of utilizing evaluation findings to drive ongoing improvement and broader dissemination of effective practices. Rigorous data collection, analysis, and reporting will be critical to demonstrating the value of this initiative to university stakeholders and external partners.

The evaluation team designed a process to evaluate cohorts of the students biannually. This process enables the team to monitor trends and changes at the population level across campus and assess the outreach, effectiveness, and impact of the app. In the first cohort, students who are new to the campus (ie, freshman, transfer, and first-year medical students) will be invited to enroll in the assessments. They will be required to provide informed consent before participating and will be compensated for their time and engagement in the quantitative and qualitative assessments (Multimedia Appendix 3).

**Table 1 table1:** A summary of the evaluation plan for the mental health and wellness app (Willow).

Evaluation domains	Outcomes	Key performance indicators	Data sources and collection method
Campus services awareness, accessibility, and utilization	Improving access to mental health resources, improved efficiency of use of resources for individual psychological counseling, referral to the app by counseling and psychological services & health and wellness providers, improved utilization of on-campus services	Satisfaction, in-app services usage, Counseling and Psychological Services usage, effectiveness and relevance of the app, utilization of campus services	App analytics, in-app rating systems, in-app surveys and questionnaires, focus groups; interviews with counseling and psychological services & health and wellness providers
Student mental health	Reducing stigma, increasing peer support, improving mental health, improving emotional self-awareness, decreasing loneliness	Trend of improved score in mental health surveys, loneliness score, social connectedness on campus	App analytics, in-app surveys and questionnaires, focus groups
Serious mental illness	Detecting and predicting serious mental illness	Detect serious mental illness	App analytics, in-app surveys, and questionnaires
Student engagement and provider engagement	Increasing engagement with the app, increased use of features and services provided by the app, increased levels of awareness and utilization of the variety of resources and support available	Adoption rates, number of users, frequency of use, duration of use sessions, referral rates from providers	App analytics, in-app surveys and questionnaires, focus groups (students/providers)
App/platform usability and effectiveness	Continued development of app roadmap and milestones, plan for long-term sustainability to support continued deployment and improvement of the app	Daily, weekly, monthly active users, satisfaction rates, acceptability, and user-friendliness scores	In-app rating systems, in-app surveys and questionnaires to collect feedback, focus groups

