### Process and Participants

A marketing campaign was initiated to advertise the Willo app across the campus during the first quarter of the academic year 2024-2025. The campaign included multiple channels to reach out to students so that they can download and start using the app. Participants who agree to join the research portion of the app launch will provide electronic consent within the app. All participants will be asked to complete web-based assessments through Qualtrics at baseline fall quarter of 2024 and spring quarter of 2025. Additionally, we will conduct 6 focus groups each consisting of 10 students to gather qualitative data about their feedback and experience with the app. If participants consent, they may be contacted up to twice per calendar year until graduation or departure from UCSD.

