### Data Analysis and Interpretation

#### Quantitative Analyses

Quantitative data will be analyzed using appropriate statistical software (SPSS or similar) to determine if users are gaining knowledge about the featured services and resources and if the services and resources that are being highlighted are matching with the desires of the target populations.

To assess changes in mental health and wellness outcomes within and between cohorts over time, we will conduct repeated measures analysis of variance and mixed-effects modeling. These approaches are well-suited for analyzing longitudinal data with repeated observations per participant. The primary dependent variables will include standardized scores from validated instruments measuring mental health and well-being. Independent variables will include cohort membership, time (semester), usage of the Willo app, and engagement with university support services. Interaction terms (eg, time × app usage) will be included to assess potential moderating effects.

A power analysis was conducted using a conservative estimate of small-to-moderate effect sizes, consistent with those commonly reported in similar longitudinal mental health studies. With 850 participants per cohort and repeated measurements across 8 time points, the study is adequately powered (≥80%) to detect meaningful changes in outcomes over time and between groups, assuming an α level of .05.

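### The plan asks whether app use leads to symptom reductions, but all survey participants are self-selected app users, so the planned contrasts support association only

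*Protocol article*

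**What the plan says.** All references are to the Methods of the protocol article.

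- **Question.** The first question listed under Evaluation Plan is causal: "To what extent does the use of the mobile app lead to reductions in symptoms of anxiety, depression". The same section says the biannual cohort process will let the team judge the app's effectiveness and impact, and adds: "This process enables the team to monitor trends and changes at the population level across campus".
- **Who is measured.** "Data collection methods will include pre-post surveys of app users to assess changes in knowledge regarding campus resources". The first cohort is new arrivals: "students who are new to the campus (ie, freshman, transfer, and first-year medical students) will be invited to enroll in the assessments".
- **How they enter.** Process and Participants describes a marketing campaign: "The campaign included multiple channels to reach out to students so that they can download and start using the app". It continues: "Participants who agree to join the research portion of the app launch will provide electronic consent within the app". Surveys are in fall 2024 (baseline) and spring 2025. Those who agree may be recontacted up to twice a year until they leave.
- **Analysis.** Quantitative Analyses names repeated-measures ANOVA and mixed models with cohort, time, app usage and engagement with support services as predictors. It adds: "Interaction terms (eg, time × app usage) will be included to assess potential moderating effects". Power is stated for 850 participants per cohort and 8 time points.

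No unexposed, waitlist or pre-launch group is described. As of March 2025 nothing had been analysed.

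**The concern.** A causal question needs a contrast between exposure and its absence that other things do not also explain. Two contrasts are on offer, and they fail for different reasons.

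1. **Pre-post change.** Everyone surveyed is on the app, so time since starting the app runs alongside time at university. The Introduction itself describes that transition as stressful and able to bring on or worsen mental health problems. In the first year the change also runs from fall to spring.
2. **Time × app usage.** This removes any shift shared by all users. What is left compares students who chose to use the app more or less. Need, motivation and changing symptoms can all drive use. The plan presents the term as assessing moderation, although it is the only within-sample contrast that bears on the first question.

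The Evaluation Plan intends to use the data to obtain continued funding and to scale the programme. An association read as an effect would feed directly into that decision.

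**Working it through.** **The plan's own figure.** The article states at least 80% power with 850 per cohort, 8 time points and α = .05. It gives no numeric effect size, correlation or dropout, so the figure cannot be reproduced exactly. It is plausible. For two groups of 850 measured once, two-sided, power = Φ(d·√(850/2) − 1.96):

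- d = 0.136: Φ(2.80 − 1.96) = 80%
- d = 0.2: Φ(4.12 − 1.96) = 98.5%

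Power is not in dispute. The question is what a significant result would mean.

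**Identification of pre-post change.**

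- Two waves, with columns for intercept, spring and app exposure, give rows (1,0,0) and (1,1,1). The rank is 2 of 3, so time and exposure are the same column.
- Eight waves, with columns for intercept, spring indicator, years on campus and years since starting the app, give rank 3 of 4. The spring indicator is now separable. The last two columns are still identical.
- Four such cohorts with three cohort indicators give rank 6 of 7. The same pair remains inseparable.

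This assumes that each cohort of new students starts the app around arrival. Scatter in start dates would break exact collinearity, but start dates are self-chosen too.

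**Size of a false pre-post result, true app effect zero.** Assumed inputs: within-person correlation 0.6 and a common shift of 0.1 SD. SD of change = √(2 × (1 − 0.6)) = 0.894.

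- n = 600: z = 0.1 × √600 / 0.894 = 2.74; Φ(2.74 − 1.96) = 78%; simulation with 2,000 replicates gives 79%
- n = 850: z = 0.1 × √850 / 0.894 = 3.26; Φ(3.26 − 1.96) = 90%; simulation gives 90%

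Under a common shift alone, the time × usage test stays at about 5%.

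**Size of a false time × usage result, true app effect zero.** Assume a latent trait correlated a with usage and b (in absolute value) with symptom change. The spurious correlation is a × b, and the expected z is about a × b × √n.

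| a / b | spurious r | z, n=600 | falsely significant | z, n=850 | falsely significant |
|---|---|---|---|---|---|
| 0.2 / 0.2 | 0.04 | 0.98 | about 16% | 1.17 | about 21% |
| 0.3 / 0.3 | 0.09 | 2.20 | 61% | 2.62 | 75% |
| 0.4 / 0.4 | 0.16 | 3.92 | 98% | 4.66 | over 99% |

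The first row uses the normal approximation; the other two are simulated. The correlations come from no part of the article and are shown as a range. The sample sizes 600 and 850 are the survey responses to date and the planned cohort. The 600 are responses before the second round, not completed pre-post pairs.

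**The case against.** Several stronger readings are tempting, and the article does not support them.

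- **A reader might infer that season can never be separated from the app.** The article plans 8 time points and several cohorts, so a repeating fall/spring effect could be separated in later years. A seasonal shift common to all users also does not bias time × usage. Adjustment to university is what remains inseparable in pre-post change.
- **A reader might infer that the sample has no low-exposure students.** Consent is in the app but the surveys are in Qualtrics and paid, so a student can consent, answer and hardly use the app. Usage may run down to near zero. Who is low is still self-chosen.
- **A reader might infer that the model ignores help-seeking.** Engagement with support services is listed. Random subject effects would also absorb stable differences in level, though not differences in change. And since raising service use is a stated aim of the app, conditioning on it may remove part of any effect.
- **A reader might infer that a false positive is more likely than not.** That holds at 0.3/0.3 but not at 0.2/0.2, and the article gives no basis for choosing.
- **A full covariate list may sit in an analysis plan that is not shown.** That is fair, and its absence is not the point. No such list would turn the stated question into one that this sample answers without strong assumptions.
- **The evaluation is adaptable and aims mainly at awareness and use of resources.** This is true, and the symptom question is not labelled primary. It is nevertheless the first question listed, and effectiveness is claimed.

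**Conclusion.** The concern holds in this form: the stated causal question and the effectiveness and impact claims go beyond what the described data can show. Pre-post change cannot be separated from adjustment to university, nor from season in the first year. Time × usage is an association open to selection and reverse causation.

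The false-positive rates depend on the assumed trait correlations, the 0.1 SD shift and the within-person correlation of 0.6, and should be read as illustrations over a range. The design facts do not depend on them.

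The campus population-level claim has a related limit: the survey sample is consenting app users, so its trends describe them unless weighted. No result is yet affected, because no analysis had been done when the article was written.

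**What to change.** 1. **Reword.** State the first question, and the effectiveness and impact claims, as change among consenting app users and its association with app use. Limit population-level survey claims to the consenting users sampled, unless the data are weighted to enrolment counts by student type.
2. **Report time × usage as an adjusted association.** Use logged use before each assessment. Add baseline PHQ-8, the generalized anxiety scale, barriers to care (BCC, BACE-3), CECA and student type, each × time. Give a second version without service engagement. Splitting usage into between-person and within-person parts adds little with two waves if use before baseline is near zero.
3. **Once later waves exist, add fall-to-fall change as a sensitivity analysis.** It removes season but still contains a year of adjustment to university, so it should not be presented as the app's effect.

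The cost is a weaker stated conclusion and a little more analysis. The covariates are already in the survey battery or known at entry. Surveying new students who do not use the app would supply a comparison in later cohorts, but it needs extra resources and is optional. This fix does not depend on it.

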### Ethical Considerations

This evaluation plan, which is described in more detail below, is approved by the UCSD institutional review board (approval 810254). Data will be collected using unique participant ID numbers that are based on the order of completion and will not be connected to any identifiable information about individual users. The app contains a digital consent form that participants complete before starting study activities. They receive an emailed copy and can access a video walk-through of the consent process. With rolling recruitment, participants can take time to decide and consult with the study team. Focus group members receive individual consent forms after eligibility confirmation. All consent forms are stored on a secure UCSD server accessible only to approved study coordinators. The consent mentions that participants can opt out at any time, and their deidentified data might be used for other studies without their consent. Participants have the opportunity to earn a maximum of US $25 per quarter for completing the surveys. Participants who take part in the focus groups will receive US $60. All incentives will be in the form of digitally delivered Amazon gift cards.

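### The plan claims to monitor population-level change across campus, but surveys only students who installed the app and consented in it, and lists no source of campus-wide service-use counts

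*Protocol article*

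**What the plan says.** All references are to the protocol article.

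- **The claim.** Evaluation Plan, on the twice-yearly cohorts: "This process enables the team to monitor trends and changes at the population level across campus and assess the outreach, effectiveness, and impact". The Methods part of the Abstract makes a similar campus-wide claim.
- **Who is surveyed.** Evaluation Plan: "Data collection methods will include pre-post surveys of app users to assess changes in knowledge regarding campus resources", among other topics.
- **How students enter.** Process and Participants describes a marketing campaign that leads students to download the app, and then: "Participants who agree to join the research portion of the app launch will provide electronic consent within the app". Ethical Considerations confirms that the consent form sits in the app.
- **Which students.** Evaluation Plan: "In the first cohort, students who are new to the campus (ie, freshman, transfer, and first-year medical students) will be invited to enroll". Results says that collection will be repeated with every cohort.
- **Service use.** The Objective in the Abstract makes greater use of campus resources the app's aim. The first row of Table 1 gives these indicators: "Satisfaction, in-app services usage, Counseling and Psychological Services usage, effectiveness and relevance of the app, utilization of campus services". Its sources are: "App analytics, in-app rating systems, in-app surveys and questionnaires, focus groups; interviews with counseling and psychological services & health and wellness providers".
- **Reach.** The engagement row of Table 1 lists "Adoption rates, number of users, frequency of use, duration of use sessions, referral rates from providers" and names no denominator.
- **Health-record data.** The Abstract and Discussion mention a link between the app and the student health record. Using data from both is presented as a long-term objective, and Table 1 does not list the record as a source.

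**The concern.** The stated target is the campus population. The sample is a self-selected subset of it: students who responded to a marketing campaign, installed the app and then agreed to research. No survey of students without the app, random or census sample, or weighting to enrolment is described. Two inferences then fail.

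1. **Trend between cohorts.** If the kind of student who installs and consents changes from one cohort to the next, survey means move even when the campus does not.
2. **Change among users read as change on campus.** The surveys say nothing about students who never installed the app, so the campus change cannot be recovered from them.

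The gap matters most for service use, which is the app's stated aim. Table 1 commits to indicators of counseling and campus-service use, but its sources are in-app data, focus groups and provider interviews. The Evaluation Plan intends to use the results to secure continued funding and to show value to university stakeholders, so an overstated campus claim would have practical consequences.

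**Working it through.** The point concerns the sampling frame and the data source, so no figure in the article needs correcting. The first two steps set the text side by side. The last three show size, using assumed inputs where stated.

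**Step 1: target against frame.** Target: the campus (Evaluation Plan). Frame: app users (Evaluation Plan), who consent in the app (Process and Participants; Ethical Considerations), drawn in the first cohort from new students only. Repeating the process with later cohorts widens the range of class years, but every cohort still consists of consenting installers.

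**Step 2: Table 1 sources against the service-use indicators.**
- App analytics record what happens in the app, not visits to a service.
- In-app ratings and surveys give reports from app users.
- Focus groups and provider interviews are qualitative and yield no rate.

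None of these gives a count of service use over all students.

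**Step 3: sample size does not help.** Quantitative Analyses states at least 80% power with 850 participants per cohort, 8 time points and α = .05. It gives no numerical effect size, correlation or attrition, so the figure cannot be reproduced exactly. As a plausibility check, take two cohorts of 850 at one time point. The effect detectable with 80% power is (1.96 + 0.842) × √(2/850) = 0.136 SD. The stated power is plausible for small effects. Precision of that order also means that a modest selection shift would be detected and could be read as a trend.

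**Step 4: false trend from a changing mix (assumed inputs).** Let campus prevalence of a symptom be P = 30% in both cohorts, and let r be the relative chance of joining for symptomatic students. Then

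sample prevalence = P·r / (P·r + 1 − P).

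- r = 1.00: 0.300 / 1.000 = 30.0%
- r = 1.25: 0.375 / 1.075 = 34.9%
- r = 1.50: 0.450 / 1.150 = 39.1%

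If r moves from 1.00 to 1.25 or 1.50 between cohorts, prevalence appears to rise by 4.9 or 9.1 points with no change on campus. The 95% half-width for one cohort of 850 is 1.96 × √(0.3 × 0.7 / 850) = 3.1 points. For a difference between two such cohorts it is √2 × 3.1 = 4.4 points. Both false trends exceed it.

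**Step 5: dilution (assumed inputs).** With a share c of students using the app,

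campus change = c × (change in users) + (1 − c) × (change in other students).

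Take 0.20 SD in users and 0 in others:

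| c | Campus change |
|---|---|
| 5% | 0.01 SD |
| 10% | 0.02 SD |
| 20% | 0.04 SD |
| 50% | 0.10 SD |

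Reading the user change as the campus change overstates it by a factor of 1/c, for example five-fold at 20%. The article gives no value for c.

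**The case against.** The strongest reply is that the four evaluation questions ask about symptoms with app use, downloads and active use, integration, and lessons learned. None asks for a campus trend, and population health is framed as a long-term goal. That is fair, and it makes a change of wording largely sufficient. The sentence claiming population-level monitoring is still in the article, and the Abstract echoes it.

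Other replies stand in part:

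- **Within-person change.** Quantitative Analyses plans models of change within participants as well as between cohorts. A shifting mix of consenters biases the between-cohort comparison; it does not by itself bias change within the same students. Step 4 is limited accordingly.
- **Low users.** A reader might infer that the cohorts contain no contrast in use at all. The article does not support that. Students who installed the app and barely used it can be in the sample, and app usage is a model term. They are not, however, students who never installed it.
- **Reach.** A reader might infer that reach cannot be measured. App Usage Analytics plans aggregate counts of active users and does not limit them to survey participants. Only the denominator is unstated, and an adoption rate implies one.
- **Incentives.** "Participants have the opportunity to earn a maximum of US $25 per quarter for completing the surveys". A reader might infer that payment inflates the active-user counts. Payment is for surveys completed in Qualtrics, not for app use, and the article gives no total number of users from which a share could be calculated.
- **Visit records.** Table 1 is a summary, and Logic Model names access to student data as a critical input. It would go too far to say that service use will rest on self-report and clicks alone. What can be said is that the sources actually listed do not include a campus-wide count.

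**Conclusion.** The point holds in this form: the article claims a property, monitoring of population-level change across campus, that its survey design does not have, and the sources it lists for service use do not supply the missing campus-wide measure. This is a mismatch between statements in the article, not a detail left to a fuller document.

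The size cannot be fixed from the article, because neither app coverage nor the selectivity of consent is given. Under the assumptions in steps 4 and 5, the false trend between cohorts is about 5 to 9 points, and the campus effect is between one twentieth and one half of the user effect. These are illustrations. The second applies only if a change in users is reported as a change on campus, a calculation the article does not itself propose.

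The point does not extend to within-person change among users, to payment, or to counts of app users. It is worth correcting. Results states that no analyses had been performed as of March 2025, so the change can still be made before any findings exist.

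**What to change.** 1. **Restate the claim** in the Evaluation Plan, and its echo in the Abstract, so that survey conclusions, including trends between cohorts, apply to consenting app users only.
2. **For any campus-level statement on service use or reach, add a campus-wide source:** aggregate quarterly counts of counseling and health-service visits from the campus health partner already in the project, including quarters before the fall 2024 launch where available. Use registrar enrolment as the denominator, for adoption as well.
3. **Report these counts descriptively,** or as an interrupted time series if enough quarters exist. The time series is optional, since whether enough pre-launch quarters are available is not known from the article.

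Aggregate counts need no linkage to individuals, so they fit the statement in Ethical Considerations that evaluation data will not be tied to identifiable information. The cost is a narrower survey claim, one aggregate data request and possibly some delay. If the request cannot be met, step 1 alone removes the unsupported claim, and campus-level conclusions on service use should then not be drawn.
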